### Study Design and Sampling Technique

This study used a cluster-assigned quasi-experimental design with pretest and posttest assessments in both control and intervention groups. The cluster unit for this study was the village, which was not randomized because the research team aimed to implement the intervention across all villages within a selected subdistrict, where the subdistrict leader would serve as a role model to encourage the community to improve malaria awareness. To obtain a representative sample, the research team randomly selected 4 of the 22 subdistricts, of which 2 were assigned as the intervention groups and 2 served as the control groups. The first 3 subdistricts each had 6 villages, and the fourth subdistrict had 7 villages; therefore, a total of 25 villages participated in the study, representing about 16% of all the villages in the district. Of these, 13 villages were assigned to the intervention group, while 12 villages formed the control group. The number of sampled households selected from each village was proportional to the number of households in that village. Within each selected village, households were randomly sampled to serve as an experimental unit as indicated in Figure 2.

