### Independent Variables of the Study

This study considers demographic and environmental factors as independent variables. Demographic variables include gender, age, education level, occupation, and socioeconomic status (SES). Respondents’ SES will be measured based on ownership of durable assets such as a television, refrigerator, car, electricity, telephone, and radio; the number of bedrooms; and home infrastructure conditions such as access to drinking water sources and the presence of water channels around the house [68]. Using principal component analysis, respondents’ SES will be categorized into 5 quantiles ranging from the lowest (quantile 1) to the highest (quantile 5) [69]. Environmental variables in the study include the location of the residence, categorized as rice fields, coastal areas, or hilly areas, and accessibility to villages, classified as easy, moderate, or difficult to access. Additionally, the study considered proximity to health facilities, including the type and distance of the nearest health facilities. For secondary data from the health center, patient records from 2013 to 2023 were reviewed for all patients with suspected malaria, and positive or negative cases were confirmed based on laboratory examination results. The number of malaria cases based on gender, age group, type of *Plasmodium*, time (year and month), location of residence, and type of treatment and the number of deaths since the period under review were collected from the 4 selected health centers.

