### Statistical Analysis

All statistical analyses will be conducted using SPSS version 27 (IBM Corp), and *P* values <.05 will be considered statistically significant.

For the first outcome variable, descriptive statistics will be used to summarize participants’ sociodemographic characteristics and environmental variables including gender, age group, SES, education level, family size, distance to the nearest health facilities, village accessibility, and household location. A chi-square test will be applied within each study group (intervention and control) to evaluate the association of basic malaria understanding, basic malaria knowledge, the level of malaria knowledge, and the level of malaria awareness before and after the intervention. Unpaired sample *t* tests will be used to investigate the statistical differences. Comparisons will be performed within groups (pre- and postintervention) and between groups to determine the impact of the intervention [61]. Furthermore, a binary logistic regression model will be used to identify the potential factors associated with malaria awareness in both the intervention and control groups [39].

For the second outcome variables, descriptive statistics will be used to summarize participants’ sociodemographic and environmental characteristics including gender, age group, SES, education level, family size, distance to the nearest health facilities, access to village, and household location for both study groups. A chi-square test will be used to evaluate the association between AMTSB and the sociodemographic and environmental characteristics of participants. Unpaired samples *t* tests will be used to assess the statistical differences. Comparisons will be conducted within and between groups for both pre- and postintervention periods. Moreover, binary logistic regression analysis will be used to identify predictors associated with AMTSB among participants in both study groups [41]. Only predictors that demonstrate statistically significant differences (*P*<.05) will be retained in the final model.

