Despite its strengths, this study has several limitations. First, village selection was not randomized for the control and intervention groups, which may introduce potential selection bias. However, the allocation strategy ensured that the distribution of villages between study groups was comparable in terms of malaria endemicity, and the intervention was designed to maximize its impact by including all villages within a selected subdistrict. Second, most of the data collected in this interventional study relied on self-reported responses from participants, covering aspects such as general malaria knowledge, symptoms, diagnosis, and prevention measure knowledge. This reliance on self-reported data introduces the potential for recall bias. However, to mitigate this limitation, all MPMP were directly observed by RAs during data collection, improving the reliability of reported behavioral measures.

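### Campaign impact is read from separate unadjusted within-group and between-group tests; no stated estimate combines the two contrasts or adjusts for the covariates collected, although arms were not randomized

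*Protocol article*

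**What the plan says.** The Study Design and Sampling Technique section describes a quasi-experiment with surveys before and after the campaign. On assignment it says: "The cluster unit for this study was the village, which was not randomized because the research team aimed to implement the intervention across all villages". The team "randomly selected 4 of the 22 subdistricts, of which 2 were assigned as the intervention groups and 2 served as the control groups", and no random allocation of those four to arms is described. The result was that "13 villages were assigned to the intervention group, while 12 villages formed the control group". The limitations paragraph of the Discussion concedes that "village selection was not randomized for the control and intervention groups, which may introduce potential selection bias", and answers with similar endemicity and the inclusion of every village in a chosen subdistrict.

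The Phase IV (Evaluation Stage) section adds that the people interviewed at the two surveys need not be the same.

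For outcome 1 (malaria awareness), the Statistical Analysis section names chi-square tests within each arm and unpaired t tests, and then states: "Comparisons will be performed within groups (pre- and postintervention) and between groups to determine the impact of the intervention [61". Regression has a separate job: "a binary logistic regression model will be used to identify the potential factors associated with malaria awareness in both the intervention and control groups". Outcomes 2 (appropriate treatment seeking), 3 (prevention knowledge) and 6 (prevention practice) repeat the unpaired t tests, the within-arm and between-arm comparisons, and a logistic model to find predictors or risk factors. For outcome 2, predictors stay in the final model only if P<.05. The abstract agrees: chi-square for score differences, regression for risk factors.

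**The concern.** Without random allocation, the arms can differ in schooling, wealth, distance to care and village access before the campaign starts. Two features of the plan leave the effect estimate exposed to this.

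- **No combined contrast.** Within-arm change and between-arm difference are tested separately. Neither is the campaign effect in a two-group before/after design. That effect is the difference between the arms in their change, and no such estimate is stated.
- **No adjustment.** The demographic and environmental variables listed under Independent Variables of the Study are used for description, tests of association and factor-finding models. No passage puts arm, survey wave or their interaction into a model, or gives an adjusted campaign effect.

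A between-arm test at the post-survey would carry any fixed imbalance. A comparison of changes would be free of a fixed imbalance, but not of a change in who was interviewed that went differently in the two arms. What is at stake is the headline claim that the campaign worked, in a study meant to inform malaria policy.

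**Working it through.** **The plan's own figure.** From the Sample Size Calculation section: p = 0.488, Z = 1.96, d = 0.05.

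- n0 = 1.96² × 0.488 × 0.512 / 0.05² = 383.9, so 384
- 384 × 2 = 768
- 768 × 1.15 = 883.2, so 884, or 442 per arm

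This reproduces. It is a precision calculation for one proportion and does not bear on which contrast estimates the effect.

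**Illustration 1: fixed imbalance, post-survey contrast only, no campaign effect.**

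From the documents: overall awareness 48.8%; 894 respondents.

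Assumed: equal split (447 per arm); one binary covariate with odds ratio 3 for awareness and prevalence about 45%; imbalance between arms of 10 or 20 points; two-sided 5% test; no clustering.

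1. Awareness by covariate level: 0.367 and 0.635. Check: 0.55 × 0.367 + 0.45 × 0.635 = 0.488, and the odds ratio is (0.635/0.365)/(0.367/0.633) = 3.0.
2. Risk difference = 0.635 − 0.367 = 0.268.
3. Bias = imbalance × risk difference: 10 × 0.268 = 2.7 points; 20 × 0.268 = 5.4 points.
4. SE of the post-survey difference = √(2 × 0.488 × 0.512 / 447) = 3.34 points.
5. With shift δ = bias/SE, the rejection rate is Φ(δ − 1.96) + Φ(−δ − 1.96).

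| Imbalance | Bias | δ | False-positive rate |
|---|---|---|---|
| 10 points | 2.7 | 0.80 | about 13% |
| 20 points | 5.4 | 1.60 | about 36% |

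For odds ratios from 2 to 4 over the same imbalances, the bias runs from 1.7 to 6.7 points and the rejection rate from about 8% to 51%.

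**Illustration 2: what happens to the difference in change.** With the same fixed imbalance, the arms differ by 2.7 or 5.4 points at both surveys, so the difference in change is 5.4 − 5.4 = 0 (or 2.7 − 2.7 = 0). Bias reappears only if the covariate mix moves differently in the two arms between surveys. A net shift of s points then gives a bias of s × 0.268; for s = 10 that is again 2.7 points. The documents give no basis for a value of s.

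**Precision of the two contrasts**, at the planned 442 per arm per survey, clustering ignored:

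- Post-survey difference: √(2 × 0.488 × 0.512 / 442) = 3.4 points
- Difference in change: √(4 × 0.488 × 0.512 / 442) = 4.8 points
- Detectable with 80% power, (1.96 + 0.84) × SE: 9.4 and 13.3 points

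**The case against.** **The baseline is not ignored.** The abstract bases improvement on before/after differences in both arms, and the analysis plans between-arm comparisons at both surveys for outcomes 2, 3 and 6. A fixed imbalance would show at baseline, and within-arm tests are not affected by it. This stands. A reader might infer that every measured difference between the arms will be counted as campaign effect, or that the 13% to 36% error rate describes the planned analysis. The documents support neither: those rates belong to a post-survey-only contrast under assumed inputs, and a fixed imbalance cancels in a difference in change. What remains is that this difference is never stated as the estimate, and that respondents may change between waves.

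**Model terms may be left to an analysis plan not shown.** This stands in part. The phrase about both groups could describe a pooled model that includes arm. But the article names the comparisons that determine impact and gives regression another purpose. For outcome 2 its P<.05 retention rule could remove a confounder, or arm itself.

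**The wording about impact appears only for outcome 1.** Correct. For outcomes 2, 3 and 6 the point rests on the same set of tests, not on an express statement.

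**No imbalance is shown.** Also correct. Terrain appears balanced: the campaign health centres, Baing and Mahu, are one coastal and one hilly, as are the other two. Schooling, wealth, distance and access are not shown to be balanced.

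A reader might also infer that occupation was dropped from the analysis, since the listed characteristics omit it. Those lists are open-ended and describe summary tables, so this does not follow.

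**Conclusion.** The point holds as a choice that should be fixed. For outcome 1 the plan states, and for outcomes 2, 3 and 6 it implies, that impact is judged from separate unadjusted comparisons in a study whose arms were not randomly assigned. No stated estimate joins the before/after and arm contrasts, and the covariates collected do not enter the effect.

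The size of any bias cannot be derived from the documents. The figures of 2.7 to 5.4 points and about 13% to 36% show what a post-survey-only reading could do under the stated assumptions; they do not forecast this study's error rate.

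The point falls short of a fatal flaw. Baseline comparisons are planned, non-random assignment is disclosed, and with two subdistricts per arm no covariate adjustment can remove unmeasured differences between subdistricts.

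**What to change.** For outcomes 1, 2, 3 and 6, state that the campaign effect comes from one model per outcome, fitted to all respondents at both surveys. It should contain:

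- arm, survey wave and the arm-by-wave interaction
- the covariates under Independent Variables of the Study, kept whatever their P value; the P<.05 retention rule for outcome 2 should not apply to this model

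Report the adjusted difference in change (percentage points for proportions, mean points for scores) with a 95% confidence interval that allows for clustering by village. State beside it that only two subdistricts were assigned per arm, so confounding at that level remains. Keep the chi-square and t tests as descriptive, and the factor-finding regressions as separate analyses.

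The cost is wording and analysis time, since the covariates are already collected. There are three downsides:

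- records with a missing covariate are lost, unless handled otherwise
- the standard error is wider than for the post-survey contrast, about 4.8 against 3.4 points before clustering
- both surveys are complete and papers are being drafted, so the change must be labelled as made after data collection

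### Keeping only predictors with P<.05 in the final AMTSB model exaggerates the odds ratios it reports; it can also distort a group comparison if study group is in that model

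*Protocol article*

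**What the plan says.** The rule appears in the Protocol article, Methods, Statistical Analysis, in the paragraph on the second outcome: "Only predictors that demonstrate statistically significant differences", with P<.05 as the limit, stay in the final model. It is stated for AMTSB only; the paragraphs on the other outcomes do not repeat it. Under Outcome Variables the first seven outcomes are primary, so AMTSB is a primary outcome.

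The same paragraph gives the regression its purpose: "binary logistic regression analysis will be used to identify predictors associated with AMTSB among participants in both study groups". It lists the participant characteristics to be summarised and related to AMTSB: "gender, age group, SES, education level, family size, distance to the nearest health facilities, access to village, and household location". The group comparison is a separate sentence placed after the chi-square and unpaired t tests: "Comparisons will be conducted within and between groups for both pre- and postintervention periods".

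The section on independent variables says: "This study considers demographic and environmental factors as independent variables". Neither study group nor survey period is listed there.

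On allocation, Study Design and Sampling Technique describes the village as the cluster unit, "which was not randomized because the research team aimed to implement the intervention across all villages within a selected subdistrict". The limitations in the Discussion concede that "village selection was not randomized for the control and intervention groups, which may introduce potential selection bias".

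**The concern.** A predictor kept because its P value fell below .05 is kept partly because its estimate happened to be large in this sample. The odds ratios in the final table are therefore too far from 1 on average, and the usual intervals treat the model as if it had been fixed in advance. True predictors of moderate strength disappear, and a reader will take their absence as evidence of no association. This damages the regression's own declared aim, whether it is pooled over groups or fitted within each.

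A second risk is conditional. If study group is among the terms, the rule can remove covariates that are individually non-significant but differ between groups, or remove the group term itself. A P value does not measure confounding. In a non-randomised comparison, a campaign effect read from the reduced model could then carry bias that the full model would have removed.

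**Working it through.** **The plan's own figures.** No figure is stated for the AMTSB model. The only design figure is the sample size, which reproduces with 0.05 used as an absolute margin: 1.96² × 0.488 × 0.512 / 0.05² = 383.9, rounded to 384; × 2 = 768; × 1.15 = 883.2, rounded up to 884. The Results section reports 894 respondents. I use 894 for a pooled single-round model and 894 / 2 = 447 for a model fitted in one group.

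**Assumptions.** The documents give no predictor effects, imbalances or AMTSB rate. I assume eight independent binary predictors, each with true odds ratio 1.25. In the simulations, selection is backward elimination at two-sided .05; the article does not name the procedure.

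**Part 1: no group term.** A closed-form approximation shows the mechanism. With each predictor at 50% prevalence and the outcome at about 50%, SE(log OR) ≈ √(16/n). The true log OR is ln 1.25 = 0.223.

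- n=447: SE = √(16/447) = 0.189. A predictor is kept only if |log OR| exceeds 1.96 × 0.189 = 0.371, that is, an estimated odds ratio above 1.45 (or below its reciprocal). The chance of this is P(Z > (0.371 − 0.223)/0.189) = P(Z > 0.78) = 0.2175, plus 0.0008 in the wrong direction. Expected number kept: 8 × 0.2183 = 1.75. Mean log OR when kept: 0.223 + 0.189 × 0.294/0.2175 = 0.479, an odds ratio of about 1.61. Coverage when kept: (0.2175 − 0.025)/0.2183 = 0.88.
- n=894: SE = 0.134 and the threshold odds ratio is exp(0.262) = 1.30. The chance of being kept is P(Z > 0.292) = 0.385. Expected number kept: 8 × 0.385 = 3.1. Mean log OR when kept: 0.223 + 0.134 × 0.382/0.385 = 0.356, an odds ratio of about 1.43. Coverage when kept: (0.385 − 0.025)/0.385 = 0.935.

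Simulation of the whole selection agrees:

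| n | kept of 8 | mean OR of those kept (true 1.25) | coverage |
|---|---|---|---|
| 447 | 1.6 | 1.66 | 86% |
| 894 | 2.8 | 1.45 | 93% |

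A second run gave 1.8, 1.64 and 86% at n=447, and 3.0, 1.43 and 94% at n=894. The full model's coverage at n=447 was 95%. On the log scale, ln 1.66 = 0.507 against 0.223, so at n=447 the surviving effects are more than doubled.

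**Part 2: group term present and forced in, one survey round, no true group effect.** n=894, 1,500 data sets per setting, nominal 5%.

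| Assumed confounders | Full model rejects | After P<.05 retention |
|---|---|---|
| 5, OR 1.25, prevalence 57% vs 43% | 5.2% | 9.5% |
| 4, OR 1.3, 60% vs 40% | 5.5% | 12.1% |
| 6, OR 1.25, 60% vs 40% | 4.9% | 17.2% |

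An independent repeat gave about 11%, 11% and 15% after selection.

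A different set-up shows when the harm fades (n=884, eight continuous covariates, true group OR 1.4):

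- Covariate OR 1.1 per SD, groups 0.3 SD apart: 5.8 of 8 dropped, log-OR bias +0.11, mean SE 0.142 against an actual SD of 0.164, coverage 84.4%. Full model: bias 0.00, coverage 93.6%.
- Covariate OR 1.2, 0.3 SD apart: bias +0.07, coverage 90.2%.
- Covariate OR 1.1 or 1.2, only 0.1 SD apart: bias about +0.03, coverage 94.8% to 96.4%.
- Covariate OR 1.5, or no imbalance: almost no bias, coverage 93.8% to 95.8%.

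If the group term is itself open to removal, it is dropped in 20% to 48% of these runs although its true odds ratio is 1.4.

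**Part 3: group-by-period term, two rounds of 894, same imbalance in both.** In the three settings of the table above, with group, period and interaction forced in, the null interaction was rejected in 3.9%, 5.1% and 4.7% of runs (full model) and in 3.7%, 5.0% and 4.9% (selected). The inflation disappears.

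**The case against.** The strongest reply is that the article never gives this regression the job of estimating the campaign effect. Its purpose is to find predictors, its independent variables are demographic and environmental, and the group comparison is described separately. The reference to both study groups can equally mean one model per group, which leaves no group term to delete. The limitations answer selection bias with comparable endemicity and inclusion of all villages, not with regression adjustment. All of this stands. A reader might infer that the campaign's effect on AMTSB is biased and its interval too narrow; the document does not support that, because it does not define an adjusted effect in this model.

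The group-effect figures also rest on chosen inputs: confounders of equal strength, all imbalanced in the same direction. They concern one round, and they vanish for the pre/post contrast when imbalance is stable. The inflation could return if imbalance changed between rounds. The Evaluation Stage allows respondents to differ between surveys, but that case was not simulated.

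Finally, the 5% for the full model assumes independent respondents. With 25 villages and an assumed intraclass correlation of 0.02 to 0.05, an ordinary logistic group test rejected a true null in about 12% to 21% of runs. That stands too.

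None of this touches Part 1. The exaggeration there needs no group term and harms the stated aim directly.

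**Conclusion.** The point holds in a limited form. The retention rule is stated affirmatively for a primary outcome, and it exaggerates the reported predictor odds ratios whether the model is pooled or fitted per group. Under the assumed true odds ratio of 1.25, survivors average 1.66 at n=447 and 1.45 at n=894, with interval coverage of 86% and 93%. Stronger predictors would be affected less. An AMTSB rate well below 50% would raise the retention threshold and the exaggeration; the Introduction calls that rate very low but gives no figure.

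Harm to a group estimate is conditional on three things: that study group is in the model, that the effect is read from one round, and that several weak-to-moderate confounders are clearly imbalanced. Then type I error of about 10-17% is plausible. Otherwise the effect on a group term that is kept in the model is small or absent. The change is worth making because it is specific and nearly free.

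**What to change.** Delete the retention sentence for AMTSB. Report the full model with the covariates the paragraph already lists: gender, age group, SES, education level, family size, distance to the nearest facility, village access and household location. State whether the model is pooled or fitted per group. Where it is used to compare groups, include study group, period and their interaction, and keep them whatever their P values. No change of this kind is needed in the other outcomes' paragraphs, which do not contain the rule.

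The cost is a sentence or two and slightly wider intervals for some covariates: about 15 parameters on about 894 interviews per round. If AMTSB proves rare, merge categories by a rule set before the outcome is examined, not by P value. Table 1 places the final-outcome analysis in March 2025 to December 2026, so the reported model may still be open to change. The fix does not deal with village clustering, so it does not by itself guarantee a 5% error rate for a group comparison.

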#### Phase II (Baseline Phase)

After securing the necessary approvals and obtaining the recommendation letter from the relevant authorities, the research team conducted a household survey with both the intervention and control groups. Before data collection, respondents were provided with a general overview of the study, and informed consent forms were obtained before their participation. The survey aimed to assess behavioral aspects of malaria and was conducted using a questionnaire that had been modified from a previous study conducted in rural ENT Province [67]. The questionnaire consisted of 40 questions designed to collect data on key malaria-related behaviors, including general knowledge of malaria, treatment-seeking behavior, and the use of malaria prevention methods. The questionnaire was completed by either the head of the household or another household member aged 18 years or older.

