The seventh outcome variable in this study is variation in access to basic drinking water and its associated factors among rural communities in ENT Province, Indonesia. Household access to basic drinking water is defined based on the WHO Joint Monitoring Program guidelines, which classify water sources into 4 categories: no service, unimproved, limited, and basic [75]. To analyze this variable, a dichotomous classification will be used, where households will be categorized as either having access to an improved drinking water source (Yes=1) or lacking access to an improved drinking water source (No=0). This classification will help determine disparities in access to safe drinking water and identify key factors influencing these differences.

The secondary outcomes of this study are derived from the analysis of patient medical records from 4 selected health centers, along with additional data from the Department of Health, East Sumba District. The eighth outcome variable focuses on the monthly number of malaria cases recorded over the past 10 years, from 2013 to 2023. By integrating data from both health centers and the Meteorological Agency of East Sumba, this study aims to explore the impact of climatic variables on malaria case fluctuations in this region, following the methodology of a previous study [76]. This analysis will provide valuable insights into seasonal and long-term trends in malaria transmission, which could help inform future malaria prevention and control strategies.

The ninth outcome variable in this study examines the demographic variations in malaria prevalence among communities residing in hilly and coastal areas over the past 10 years (2013-2023). Among the 4 selected health centers, Baing and Nggongi Public Health centers are located in coastal areas, whereas Mahu and Kananggar Public Health Centers are situated in hilly regions. Given that vector distribution and species composition may vary between different geographic settings [77], previous studies in Indonesia have reported significant differences in malaria prevalence between coastal and hilly areas [78]. By analyzing malaria case records from these health centers, this study aims to assess regional disparities in malaria burden and determine how demographic and environmental factors contribute to these differences. This information may help tailor malaria prevention and control efforts to the specific needs of different geographic regions.

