For the sixth outcome variable, participants’ sociodemographic characteristics, environmental variables, and behavioral aspects of malaria in each group will be reported using descriptive statistics. The association between a good level of MPMP and its predictors will be investigated using chi-square tests. Unpaired samples *t* tests will be used to investigate the statistical differences. Comparations will be performed within and between groups for both pre- and postintervention periods. Moreover, binary logistic regression analysis will be performed to identify the primary risk factors influencing MPMP [73,74] among rural communities in both study groups.

For the seventh outcome variables, descriptive statistics will be used to summarize participants’ sociodemographic characteristics, environmental variables, and malaria-related behaviors based on their source of drinking water. The associations between access to improved drinking water and its predictors will be assessed using chi-square tests. Furthermore, a binary logistic regression model will be used to determine predictors influencing access to improved drinking water [75].

For the eighth outcome variable, descriptive analyses of climatic factors across different subdistricts will be performed. Data will be aggregated at the subdistrict level, and statistical estimates will be generated for each variable. Specifically, the total number of malaria cases and the average malaria incidence will be computed. Climatic variables, including maximum, minimum, and mean temperature values, will be calculated. Moreover, data from all 22 subdistricts will be analyzed, focusing on malaria cases and climatic parameters, including maximum, minimum, and average temperature values. To depict the seasonal dynamics, seasonal variations in climatic parameters and malaria cases will be plotted, covering the 2 main seasons. A time series for both predictor and outcome variables will be plotted to deliver an overall perspective. A map of malaria cases will be generated. Scatterplots will be developed to illustrate relationships between malaria cases and predictor variables, following the methods of a previous study [76].

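### Drinking-water access is a household outcome, but its implied predictors include personal traits of whichever adult answered, and the SES index partly contains the outcome

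*Protocol article*

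**What the plan says.** Under Outcome Variables, the seventh outcome (counted among the primary ones) is defined for the household: "households will be categorized as either having access to an improved drinking water source (Yes=1) or lacking access to an improved drinking water source (No=0"). Under Study Design and Sampling Technique, households are the sampled unit.

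Under Phase II (Baseline Phase), "The questionnaire was completed by either the head of the household or another household member aged 18 years or older". No rule for choosing among the adults of a household is given. Phase IV (Evaluation Stage) adds that the people surveyed may differ between rounds according to availability.

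Under Independent Variables of the Study, "Demographic variables include gender, age, education level, occupation, and socioeconomic status (SES"). SES is described as the respondent's. It is built from durable assets, number of bedrooms and home infrastructure, and the infrastructure items include access to drinking water sources. Residence location, village accessibility and proximity to health facilities are also listed.

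For the seventh outcome, Statistical Analysis describes participants' "sociodemographic characteristics, environmental variables, and malaria-related behaviors based on their source of drinking water", tests access against its predictors by chi-square, and then states that "a binary logistic regression model will be used to determine predictors influencing access to improved drinking water".

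**The concern.** All adults in a household share one water source. Gender, age, education and occupation belong to one person. These traits suit the awareness, treatment-seeking and prevention-knowledge outcomes, where the respondent's own answers are the outcome. Carried over to a household attribute, they make the covariate depend on who was interviewed: the same male-headed household is coded male if the husband answers and female if the wife does, with the same outcome. The article does not say that the head's traits are used, that respondent status is adjusted for, or that this outcome is limited to household-level predictors.

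The second problem lies in the SES index. A household with a better water source can score higher on SES because of that source, so an SES gradient in water access is partly built in.

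At stake is the list of factors that this outcome is meant to deliver. A real effect of the head's sex or schooling could be understated, missed or reversed, and the effect of SES overstated.

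**Working it through.** **Figures in the plan.** The article gives no figure for this outcome. Its only design figure, the sample size, reproduces with d read as absolute: 1.96² × 0.488 × 0.512 / 0.05² = 383.9, rounded to 384; × 2 = 768; × 1.15 = 883.2, rounded up to 884. It was not derived for drinking water and does not bear on this point.

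The documents do not say how often the head answers, how many heads are women, or how common access is. All inputs below are assumptions that show direction and range.

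**A. Gender, varying who answers.** Assume 15% female heads, access 0.50 in male-headed households and a true OR of 0.60. Access in female-headed households is then 0.60/1.60 = 0.375. The head answers with probability q; otherwise an adult of the opposite sex does.

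- Female respondents: weight 0.15q from female-headed and 0.85(1−q) from male-headed households.
- Male respondents: weight 0.15(1−q) from female-headed and 0.85q from male-headed households.

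For q = 0.75:
- Women: (0.1125 × 0.375 + 0.2125 × 0.50)/0.325 = 0.4567
- Men: (0.0375 × 0.375 + 0.6375 × 0.50)/0.675 = 0.4931
- OR = (0.4567/0.5433)/(0.4931/0.5069) = 0.86

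| Head answers in | OR by respondent gender |
|---|---|
| 100% | 0.60 |
| 75% | 0.86 |
| 50% | 1.00 |
| 25% | 1.16 |

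At 25% the two groups swap, so the OR is 1/0.8644 = 1.157. A simulation of 800,000 households gave 0.60, 0.86, 1.00 and 1.15.

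**B. Gender, another response pattern.** Assume 15% female heads and access 0.60 in male-headed households. Women answer in 90% of female-headed and 50% of male-headed households. With a true OR of 0.60, access in female-headed households is 0.9/1.9 = 0.474.

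- Women: (0.135 × 0.474 + 0.425 × 0.60)/0.56 = 0.570
- Men: (0.015 × 0.474 + 0.425 × 0.60)/0.44 = 0.596
- OR = 0.90

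A true OR of 0.50 gives 0.86 in the same way.

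**C. Education.** Assume 40% of heads educated and a true OR of 2.0, with access odds 2^0.6 (probability 0.602) if the head is educated and 2^−0.4 (0.431) if not. A proportion r of other adults share the head's value; the rest are independent.

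- P(head educated | respondent educated) = q + (1−q)[r + 0.4(1−r)]
- P(head educated | respondent not educated) = 0.4(1−q)(1−r)
- Access in each respondent group = 0.431 + that probability × (0.602 − 0.431)

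Example, q = 0.5 and r = 0: the probabilities are 0.70 and 0.20, access is 0.551 and 0.465, and the OR is 1.41.

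| Head answers in | OR, r = 0 | OR, r = 0.6 |
|---|---|---|
| 75% | 1.68 | 1.86 |
| 50% | 1.41 | 1.74 |
| 25% | 1.19 | 1.62 |

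**D. SES.** No arithmetic is needed. The water-source item is listed among the inputs to the principal component index, and the outcome is a classification of the water source. The size of the overlap depends on that item's loading, which is not given.

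**The case against.** The strongest reply is that the article never lists the regressors for this outcome. Participants' characteristics appear only in the sentence on descriptive statistics, and the personal traits come from the study-wide list, which also holds household-level variables. The questionnaire is in an appendix that is not shown and may record the head's traits or the respondent's status. A condensed article may leave such coding to the full plan. This stands as a limit: the point concerns what follows if the text is applied as written. It does not remove the mismatch, because nothing in the text points to the head's traits. It does not touch the SES overlap, which is stated outright.

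Three stronger readings are tempting and are not supported:

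- **That malaria behaviours are modelled as causes of water access.** They are named only in the descriptive sentence, and a table by water source makes no causal claim.
- **That chance patterns in who was at home would produce false determinants.** If who answers is unrelated to access, false positives stay near the nominal 5%. A spurious link would need availability to be systematically related to access, and nothing in the documents shows that.
- **That the bias has a known size.** It can be nil (the head always answers) or modest (education 1.68 to 1.86 against 2.0 when the head answers in 75%).

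The consequence is also limited. Drinking water is absent from the stated objectives and the campaign content, and its analysis describes no intervention-control comparison.

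**Conclusion.** The point holds in a limited form. The outcome belongs to the household, any adult may answer, and the only listed demographic predictors apart from SES are personal ones. Read together, these imply a model whose coefficients for gender, age, education and occupation depend on who was interviewed. As measures of household determinants they would usually be diluted. For gender they could vanish or reverse if heads seldom answer and the substitute is of the opposite sex. The ranges (0.60 to about 1.16 for a true OR of 0.60; 1.19 to 1.86 for a true OR of 2.0 when the head answers in 25% to 75% of households) rest wholly on assumed inputs.

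Only person-level covariates are exposed to this. SES, family size, location, accessibility and distance do not change with the respondent, but SES has its own defect because it includes the water source. This is a minor point about interpreting one outcome, despite its primary label, and conclusions about the campaign are not affected.

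**What to change.** For the seventh outcome:

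1. Base the main logistic model on household-level predictors: SES recomputed without the water items, family size, distance to the nearest facility, village accessibility and residence location.
2. Report personal traits only in a secondary model. Use the head's characteristics, or adjust for respondent status, if these were recorded. Otherwise label the traits as those of the respondent.
3. Replace the wording of influence with association.
4. Keep malaria behaviours in the descriptive table if wanted, but do not enter them as predictors of water access.

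The change is to analysis and wording, and the timeline runs final analysis to December 2026. The costs are that the main model loses education and occupation, and SES must be computed a second time. A head-only model would be smaller and would select households whose head was available. It is possible only if respondent status was recorded, which cannot be confirmed here and, with fieldwork finished in February 2025, may not be recoverable.
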